## 5. TREATMENT OF RESEARCH PARTICIPANTS

In this study we will provide a multidisciplinary prehabilitation program to patients that are planned to undergo endovascular or surgical revascularization for CLTI. The duration of the prehabilitation program is at least 2 weeks and consists of seven major components:

- 1) Screening of general health, signs of frailty, comorbidities, nutritional state, and performing functional and cognitive testing, by a vascular nurse practitioner or researcher at the MVE.

All patients included in the study, regardless of control or intervention group, will go through this first step of the MVE. Afterwards the patients in the intervention group start their prehabilitation program, consisting of:

- 2) Screening and provision of personalized, home-based exercises by a physiotherapist. Patients will track their daily activities in a diary.

And, if indicated:

- 3) Provision of nutritional advice by a dietician, based on the body mass index (BMI), Mini Nutritional Assessment Short Form (MNA-SF) score and the SNAQ-score. If indicated, patients will receive high protein nutrient drinks and recommendations of a high protein diet.
- 4) Comprehensive geriatric assessment (CGA) by a geriatrician.
- 5) In case of an iron deficiency anemia (haemoglobin <8,1 mmol/L for male patients and <7,4 mmol/L for female patients), patients will receive iron infusion using ferric carboxymaltose,
- 6) Assessment of self-reliance and home situation by a prearranged homecare nurse
- 7) Guidance and support for smoking cessation by a quit smoking coach.

The IC participates with the patient in the program. We performed a pilot interview study in CLTI patients and their ICs. Their advises and recommendations are incorporated in our prehabilitation program for CLTI and the POCI-study in general.

### 5.1 Investigational product/treatment

Not applicable

### 5.2 Use of co-intervention (if applicable)

There are no restrictions for participants.

### 5.3 Escape medication (if applicable)

Not applicable

## 6. INVESTIGATIONAL PRODUCT

### 6.1 Name and description of investigational product(s)

Not applicable.

### 6.2 Summary of findings from non-clinical studies

Not applicable.

### 6.3 Summary of findings from clinical studies

Not applicable.

### 6.4 Summary of known and potential risks and benefits

Not applicable.

### 6.5 Description and justification of route of administration and dosage

Not applicable.

### 6.6 Dosages, dosage modifications and method of administration

Not applicable.

## **7. NON-INVESTIGATIONAL PRODUCT**

### **7.1 Name and description of non-investigational product(s)**

Not applicable.

### **7.2 Summary of findings from non-clinical studies**

Not applicable.

### **7.3 Summary of findings from clinical studies**

Not applicable.

### **7.4 Summary of known and potential risks and benefits**

Not applicable.

### **7.5 Description and justification of route of administration and dosage**

Not applicable.

### **7.6 Dosages, dosage modifications and method of administration**

Not applicable.

### **7.7 Preparation and labelling of Non-Investigational Medicinal Product**

Not applicable.

### **7.8 Drug accountability**

Not applicable.

## 8. METHODS

### 8.1 Study parameters/endpoints

#### 8.1.1 Main study parameter/endpoint

The primary outcome of this study is LOS (Appendix 1-Uitkomstmaten).

#### 8.1.2 Secondary study parameters/endpoints

Secondary outcomes (Appendix 1-Uitkomstmaten) will be postoperative complications, hospital readmission rate, 6-month mortality, QoL of both patient and their informal caregiver (measured by using the WHOQoL-BREF), the health related QoL of patients (measured by using the EQ-5D-5L), burden on informal caregiver (using the CSI), the level of perceived SDM of the patient and their IC (using the CollaboRATE), perceived and preferred roles in DM of the patient and their IC (using the ACPS), preferred participation in SDM of the patient and their IC (using the PICS), a cost-effectiveness analysis will be performed (using the iMCQ) and a process evaluation will take place (using an effect evaluation form designed by the research group). For the forms used to measure these endpoints, see 'F1-Vragenlijsten.

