**LIST OF ABBREVIATIONS AND RELEVANT DEFINITIONS**

|                 |                                                                                                                    |
|-----------------|--------------------------------------------------------------------------------------------------------------------|
| AE       | Adverse Event                                                                                               |
| AFS      | Amputation Free Survival                                                                                    |
| AR       | Adverse reaction                                                                                            |
| ASA      | American Society of Anesthesiologists                                                                       |
| BMI      | Body Mass Index                                                                                             |
| CCI      | Charlson Comorbidity Index score                                                                            |
| CCMO     | Central Committee on Research Involving Human Subjects; in Dutch: Centrale Commissie Mensgebonden Onderzoek |
| CFS      | Clinical Frailty Score                                                                                      |
| CGA      | Comprehensive Geriatric Assessment                                                                          |
| CLTI     | Chronic Limb Threatening Ischemia                                                                           |
| CSI      | Caregiver Strain Index                                                                                      |
| DEMMI    | The ‘De Morton Mobility Index’                                                                              |
| DM       | Decision Making                                                                                             |
| DOSS     | Delirium Observation Screening Score                                                                        |
| DSMB     | Data Safety Monitoring Board                                                                                |

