## 1. INTRODUCTION AND RATIONALE

In the face of an aging population, the prevalence of CLTI among elderly persons of 65 years and older has become a major public health concern. CLTI, a severe form of PAD, is characterized by atherosclerotic occlusion of the arteries supplying the lower extremities, leading to ischemic rest pain and/or tissue damage (1). Annually, 500-1000 new cases of CLTI occur per 1 million people in Europe.

Revascularization is the primary treatment for CLTI and current guidelines advise to do this as soon as possible to prevent major limb amputation. However, the treatment of CLTI is associated with reduced QoL of both patient and their ICs, long duration of hospital stays, intensive wound care, high chance of discharge to a nursing home and places a high burden on the IC (2). Thereby, up to a quarter of the CLTI patients is at risk for major amputation despite revascularization attempts.

Recognizing the need for a strategy to minimize the risk of developing complications, diminish the LOS and increase QoL, multimodal prehabilitation has emerged as a promising preoperative approach within vascular surgery. Prehabilitation is the all-encompassing term of preoperative optimization of the patient's functional capacity and resilience, in order to reduce postoperative complications (3). Interventions include physical, mental, functional and nutritional optimization.

The decision on the treatment of CLTI should be made in a SDM process. SDM increases patients' knowledge of treatment options, initiates accurate risk perception, improves patient satisfaction and reduces undesired care in certain categories of patients (4). However, it is known that SDM is still not common practice in vascular surgery and thorough research in this field is lacking.

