### Multidisciplinary meeting

All patients will be discussed in a weekly, multidisciplinary meeting with vascular surgeons and (intervention)radiologists. Based on the type of pathology and taking in account both the imaging and the mental state, condition, frailty, V-POSSUM and comorbidity of the patient as screened during the MVE visit, consensus will be made concerning the type of treatment these patients will undergo. Regarding revascularization for CLTI there are several options:

Surgical options cover:

- endarterectomy (femoral communal artery) with or without percutaneous transluminal angioplasty (PTA) of any trajectory
- bypass
  - supragenaal, infragenaal, crural

- venous (using the great saphenous vein, small saphenous vein or arm vein) or polytetrafluoroethylene (PTFE)
- aorto-iliacal or femoral.
- may include wound debridement and minor amputation

Endovascular options cover:

- PTA of any trajectory
- with or without a drug eluting balloon
- with or without stenting
- may include wound debridement and minor amputation

Patients treated conservatively and patients requiring primary major amputations are not included in this study.

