### **8.4 Withdrawal of individual research participants**

Participants can leave the study at any time for any reason without any consequences if they wish to do so. Already collected data will be included in the study. Data regarding LOS, mortality, hospital readmission rate and complications will still be collected from the electronic patient dossier (EPD). The investigator can decide to withdraw a participant from the study for urgent medical reasons.

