### **8.7 Premature termination of the study**

This study will be terminated prematurely in case of any remarkable negative effects (complications and/or mortality) in the intervention group, compared to the control group.

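### Major amputation and amputation-free survival are named in no endpoint or analysis, and the rule on primary major amputation, read as written, excludes patients after randomisation

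*Protocol*

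**What the plan says.** The primary outcome is length of stay (Section 8.1.1). The secondary outcomes in Section 8.1.2 begin with "postoperative complications, hospital readmission rate, 6-month mortality" and continue with quality of life, caregiver burden, decision-making scales, cost-effectiveness and a process evaluation. The Summary, Section 2 and Sections 10.1 and 10.2 name no limb outcome either, and Sections 8.1.3 and 10.3 (other parameters) are marked not applicable. "Amputation Free Survival" is defined in the list of abbreviations and used nowhere else in the text at hand.

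On why timing matters, Section 1 says of revascularisation that "current guidelines advise to do this as soon as possible to prevent major limb amputation", and that "up to a quarter of the CLTI patients is at risk for major amputation despite revascularization attempts".

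On who stays in the trial, Section 8.3 (Multidisciplinary meeting) says: "Patients treated conservatively and patients requiring primary major amputations are not included in this study". Section 10 promises an intention-to-treat analysis of all patients.

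On safety, Section 8.7 says: "This study will be terminated prematurely in case of any remarkable negative effects (complications and/or mortality) in the intervention group". For patients who leave the study, Section 8.4 says: "Data regarding LOS, mortality, hospital readmission rate and complications will still be collected from the electronic patient dossier (EPD"). Section 9.4 directs the DSMB's interim data to complications.

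**The concern.** The protocol describes a move from revascularising promptly to giving time for prehabilitation, in a disease where, by its own account, prompt treatment is meant to save the limb. Limb loss is therefore the harm most directly tied to the strategy under test. At the first visit the protocol even scores the WIfI classification, partly because it estimates amputation risk, but it names no amputation outcome to set against that prediction.

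Two things are at stake. First, a trial reporting a shorter stay with no excess of complications or deaths would have no prespecified between-arm limb result to support its premise that prehabilitation is safe in these patients. Second, if a primary major amputation decided after randomisation takes a patient out of the analysis, the arms compared on length of stay are no longer the arms that were randomised. The exclusion could also depend on what happened during the preoperative period.

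**Working it through.** **Order of events (protocol text)**

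1. Inclusion is on the day after the first outpatient visit, and randomisation follows immediately (Sections 3 and 8.2).
2. The screening visit takes place within a few days, after randomisation (Sections 3 and 8.3).
3. The multidisciplinary meeting uses the findings of that screening to choose the treatment (Section 8.3). It therefore comes after randomisation.
4. The sentence on patients who are not included stands at this step. Conservative therapy is also an exclusion criterion in Section 4.3; primary major amputation is not. For either group, if the decision is made at the meeting, the sentence acts as a post-randomisation exclusion.
5. Section 10 analyses all patients as randomised. Steps 4 and 5 cannot both be followed.

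**Where would a limb lost between randomisation and revascularisation be counted?**

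- Length of stay, readmission, mortality: not as limb loss.
- Postoperative complications: on a plain reading no, because there has been no operation to follow.
- Questionnaires at 6 months: Section 8.3 times these from revascularisation, so a patient never revascularised has no defined assessment date.
- Adverse event reporting (Sections 9.2.1 and 9.2.2): yes, it could be recorded, but this is not a named comparison between arms.
- DSMB: Section 9.4 asks for complications. Section 10.4 frames the question as an increase in the arm without prehabilitation, the opposite direction from Section 8.7.

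**Precision of a new limb outcome**

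The protocol gives no planning figure for limb loss. Inputs: 300 patients (Section 4.4), taken as 150 per arm on an assumed 1:1 allocation. The rates p are assumptions; only 25% echoes a protocol figure, and there it is an upper bound for amputation despite revascularisation attempts.

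Half-width of the 95% CI for the risk difference, equal rates: 1.96 × √(2p(1−p)/150). For p = 0.10: 1.96 × √(0.18/150) = 1.96 × 0.0346 = 6.8 points.

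Power for a relative risk of 1.5, two-sided 5%: Φ{(|p₁−p₀| − 1.96√(2p̄(1−p̄)/150)) / √([p₀(1−p₀)+p₁(1−p₁)]/150)}, where p̄ is the mean of the two rates. For 10% against 15%: (0.050 − 0.0749)/0.0381 = −0.65, so about 26%.

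| Assumed rate | Events in 300, equal arms | Half-width (points) | Power, relative risk 1.5 | Rate in other arm for 80% power |
|---|---|---|---|---|
| 5% | 15 | 4.9 | 14% | 14.6% |
| 10% | 30 | 6.8 | 26% | 21.8% |
| 15% | 45 | 8.1 | 38% | 28.3% |
| 20% | 60 | 9.1 | 52% | 34.3% |
| 25% | 75 | 9.8 | 65% | 40.1% |

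**Effect of an exclusion on the primary analysis**

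Section 4.4 states 80% power for a length-of-stay ratio of 0.75 with SD 0.9 on the log scale. The standardised shift is ln(1/0.75)/(0.9 × √(2/150)) = 0.2877/0.1039 = 2.77, and Φ(2.77 − 1.96) = 79.1%, which reproduces the stated figure closely. If 2%, 5% or 10% of randomised patients were left out (assumed; 294, 285 or 270 remain), power falls to 78.2%, 77.0% or 74.7%. The loss of power is small. The issue is selection, not sample size.

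**The case against.** The strongest reply is that limb loss has several routes into the data. Section 9.2.1 records any undesirable experience, related or not. Section 9.2.2 covers events causing hospitalisation or lasting disability, and says that patients with an adverse event stay in the database and are not withdrawn. The carve-out for elective admissions does not remove the disability criterion. Sections 8.4, 8.6, 8.7 and 9.4 speak of complications without the word postoperative. Hospital cost records cover interventions over 6 months. Outcomes are referred to an Appendix 1 that is not at hand and may count amputation after revascularisation as a complication. All of this stands. A reader might infer that limb loss would be invisible or that no endpoint could count it; the documents do not support that. What remains is that no limb outcome is named as a between-arm comparison in the protocol text.

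A second reply is that the sentence in Section 8.3 only describes scope, since the Summary and Section 3 enrol patients already planned for revascularisation. That reading is possible. A reader might infer that such patients are certainly removed; the text says only that they are not included, and Section 10 points the other way. The conflict needs resolving whichever reading was meant.

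Third, Section 3 says that prehabilitation runs alongside treatment planning without delay, and Section 4.3 excludes patients needing treatment within two weeks. So a reader may not infer that the prehabilitation arm will lose more limbs. Without a limb outcome, however, that reassurance has no direct test.

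Fourth, the new outcome would be unpowered. True: power for a relative risk of 1.5 is 14% to 65% over the assumed rates. It could not establish safety on its own, but an estimate with an interval is more informative than none.

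The unused abbreviation is weak evidence either way. Overall survival and a delirium score are also defined and not used in the body.

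**Conclusion.** The point holds in this form: the protocol text names no limb outcome in any endpoint or analysis, and the rule on primary major amputation, read as written, is a post-randomisation exclusion that conflicts with intention to treat. A limb lost before revascularisation could reach the adverse event records but falls outside every named comparison.

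The size of this gap cannot be derived from the documents. It is tempting to apply the introduction's quarter to 150 patients per arm (150 × 0.25 = 37.5) and call those the uncounted events. That would be wrong: the figure is an upper bound for amputation despite attempted revascularisation, and such events may be scored as complications. The half-widths of 4.9 to 9.8 points describe how precisely the added outcome would be estimated, not how much is now missed. They rest on 1:1 allocation, equal rates in the arms and complete limb status.

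This is an inexpensive change that should be made. It closes off a possible selection bias and lets the trial examine its own safety premise. It is not a finding that prehabilitation causes harm, or that the primary analysis is invalid.

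**What to change.** - In Sections 8.1.2 and 10.2, name major amputation and amputation-free survival at 6 months from randomisation as secondary safety outcomes, in all randomised patients, including those never revascularised. For each, report the risk difference with a 95% CI, adjusted for hospital.
- In Sections 8.4 and 8.6, add limb status to the data still collected after withdrawal.
- In Section 9.4, add major amputation by arm to the data given to the DSMB.
- Reconcile Section 4.3, the Multidisciplinary meeting part of Section 8.3 and Section 10, so that a primary amputation decided after randomisation is analysed as an outcome and not treated as an exclusion. Handle conservative treatment decided after randomisation in the same way for the analysis set.
- If Appendix 1 already defines complications to include amputation, say so in Section 8.1.2 and state whether events before revascularisation count.

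Cost: one extra item from the patient record and a protocol amendment, with no added visit or procedure. The downside is one more unpowered secondary outcome, which should be presented as an estimate and not as proof of safety.

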#### 8.1.3 Other study parameters

Not applicable

### 8.2 Randomisation, blinding and treatment allocation

Randomization will be performed immediately after inclusion of a participant, either by the VNP or by the responsible researcher. Participants will be allocated to either the prehabilitation group or the control group. A variable block randomization procedure will be applied to minimize the risk of unequal group sizes and to reduce predictability of assignments. To further ensure comparability between study arms, randomization will be stratified by the participating hospital (to eliminate possible differences between hospitals). By stratifying we aim to prevent systematic imbalances and to enhance the internal validity of the trial. The randomization procedure will be carried out using the validated electronic data capture system Castor EDC. This study is not subject to blinding due to the extensive and active nature of the intervention. While blinding is not feasible, objective outcome measures and standardized assessment procedures will be used to minimize potential bias.

### 8.3 Study procedures

In this study we will provide a multidisciplinary prehabilitation program to patients  $\geq 65$  years that are planned to undergo endovascular or surgical revascularization for CLTI. The prehabilitation program is started at the MVE and will have a total duration of  $\pm 2$  weeks. This cut-off point is chosen taking in account both the time that we expect to get most optimal results from the program, and the time wherein revascularization should take place.

#### First visit to the outpatient clinic of the vascular surgeon (diagnosis)

All patients will be examined by the vascular surgeon at the first outpatient clinic visit. The WIfI score will be used to classify the patient at the time of initial presentation (see Appendix 2-Meetinstrumenten). This score for threatened lower limbs combines the three main factors that have an impact on limb amputation risk: Wound (W), Infection (I) and foot Infection (fI) (9). This score is helpful in estimating the benefit of revascularization and the risk of amputation at one year for each individual patient.

Additional research will be requested. This may include an Electrocardiogram (ECG), Ankle-Brachial Index (ABI), toe pressure in case of non-compressible vessels (common in diabetics). Imaging may be performed by duplex, or Magnetic Resonance Angiography (MRA) or Computed Tomography Angiogram (CTA). Vascular pathology will be scored using the Trans-Atlantic Inter-Society Consensus Document on Management of Peripheral Arterial Disease II (TASC-II, see Appendix 2-Meetinstrumenten) and description of the crural outflow (in 1,2 or 3 arteries) (10-12).

All patients meeting the inclusion criteria for this study and their IC receive an information map, consisting of an (patient) information folder (PIF) and an Informed consent form and are called the next day by a researcher or VNP to ask if they want to participate in the study (E1.Proefpersonen informatiebrief and E1.Mantelzorger informatiebrief).

#### Multidisciplinary Vascular surgical outpatient clinic for the Elderly (MVE)

Directly after inclusion patients will be referred to the MVE. It is important that the patient brings an informal caregiver, for example a partner, family member or close friend to optimize the (hetero)anamnesis and to make sure all information is understood and processed well. Also, hereby we can investigate the possibility of informal care, provided by friends or family. If needed, home care will already be arranged for after discharge. Written informed consent for participating in the study will be obtained by a researcher or VNP.

- *Vascular surgery Nurse Practitioner or researcher*

A trained VNP or researcher will screen all patients on baseline characteristics, signs of frailty and the presence of risk factors for delirium. Comorbidity will be scored using the V-POSSUM score, ASA-classification, Charlson comorbidity index and the Comprehensive Comorbidity Index (CCI) (Appendix 2-Meetinstrumenten). Frailty will be scored using the Clinical Frailty Scale (CFS) (13) and the Geriatric-8-score (G8-score) (14). The VNP or researcher will withdraw the Mini Mental Status Exam (MMSE) (15) to assess cognitive function. Dietary state is assessed by using the Short Nutritional Assessment Questionnaire (SNAQ-score) (16). Also, an inventory is made of available (informal) care and whether problems are expected after dismissal. Patients randomized to the intervention group, might subsequently be referred to the geriatrician, dietician and a 'quit smoking coach' if necessary.

- *Biochemistry tests*

Biochemistry tests will be performed prior to the visit to the VNP or researcher at the MVE. This will consist of: haemoglobin, haematocrit, MCV, C-Reactive Protein, leukocytes, thrombocytes, liver enzymes (ASAT, ALAT), electrolytes (sodium, potassium, chloride), albumin, MDRD, urea, creatinine, INR, lipid spectrum including cholesterol, vitamin D, vitamin B12, folium acid, transferrin, ferritin. Therefore, three blood tubes will be taken.

- *Physiotherapist*

After the visit to the VNP or researcher, patients in the intervention group will be screened by a physiotherapist. The physical state of the patient will be examined and the following tests are performed:

- Maximal inspiratory and pressure (MIP);
- The 'De Morton Mobility Index' (DEMMI)
- Gripstrength, using the hand dynamometer (JAMAR®);
- Timed Up and Go (TUG) test;
- Timed Chair-Stand test;
- Gait speed (10 Meter walking test);

Based on these results, patients are provided with their own instructions and home-based exercises (Appendix 2-Meetinstrumenten). Patients are asked to keep track of all their activities in a daily diary.

- *Optional: Geriatrician*

If indicated, patients will undergo a CGA as performed by a geriatrician to assess frailty. Based on the CGA, the geriatrician will, among other things, define preventive measures for functional decline and delirium. Patients will be referred to the geriatrician in case of:

- MMSE < 26
- TUG > 14 sec
- Previous delirium
- Polypharmacy > 4 (cardiovascular risk management medications not included)
- Alcohol consumption > 7 units per week
- G8-score < 14

- *Optional: dietician*

If indicated, a dietician will evaluate the nutritional status of the patient (using the MNA-SF score and the SNAQ-score). If indicated, they will receive high protein nutrient drinks and recommendations of a high protein diet.

- *Optional; quit smoking coach*

If indicated, patients will be referred to a 'quit smoking coach' to receive guidance in reducing nicotine abuse. They will see the patients within 3 days after referral and offer appropriate guidance on an individual basis or group therapy.

- *Optional; iron infusion*

In case of iron deficiency anemia (haemoglobin <8,1 mmol/L for male patients and <7,4 mmol/L for female patients), patients will receive iron infusion using Ferinject (ferric carboxymaltose). This will clinically take place during a day-care admission. Patients will receive a dose of 1000mg intravenous in 15 minutes.

